### Preoperative Nutritional Supplementation

Nutritional supplementation will be carried out based on the risk of malnutrition and independently of the study protocol. To identify those at risk of malnutrition, a Patient-Generated Subjective Global Assessment (PG-SGA) will be completed by the patient [39]. In case of moderate or severe malnutrition, we will refer patients to nutrition consultation. Patients referred to nutrition consultation will also complete the treatment during the follow-up period before surgery (4-6 weeks).

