**Assessment**						
	Nutritional evaluation		✓		✓	
	Quality of life		✓		✓	
	Medical history		✓			✓
	Complication rate (Clavien-Dindo)					✓
	Adverse effects			✓	✓	
	Fecal and blood sample collection		✓		✓	

At visit 0, we will review inclusion and exclusion criteria. Patients who meet the criteria will be informed about the study and assigned an ID number. The principal investigator will record and keep this number appropriately. Patient will receive the informed consent and a device to collect a fecal sample at home.

At visit 1 (baseline), if patient agrees to participate in the study, we will perform randomization. We will also evaluate nutritional status and perform the quality of life assessment. Previous medical history will be recorded, fecal sample will be obtained from the patient, and blood samples will be collected. If malnutrition is detected, we will refer the patient to nutrition consultation. Additionally, the patient will receive another device to collect the needed fecal sample at the end of the study.

Follow-up visits will be performed weekly for 4 to 6 weeks. We will use this weekly phone call to collect data about adverse effects and treatment compliance.

Closeout visit will be done at the same time as patient admission. The intervention will end at this time, and patients will return the remaining treatment to researchers. We will also pick up fecal and blood samples, evaluate the nutritional status, and assess quality of life again. Further, data about adverse effects will be collected.

The end of the study will be defined by patient discharge. We will evaluate and classify the surgery complications at this time. Data collection will include information about antibiotic prophylaxis used, length of stay, vital status, surgery performed, and final staging of the CRC according to the TNM.

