#### Nutritional Evaluation

We will use 4 anthropometric measures to evaluate nutritional status: weight, height, BMI, and body fat percentage. Nutritional status assessment will be based on the PG-SGA survey and albumin, prealbumin, total lymphocytes, and hemoglobin levels.

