Finally, we will perform a causal mediation analysis to measure the direct and indirect effects of Micodigest 2.0 on colorectal surgery complications. We will include as mediators the variables related to complications after surgery. This analysis will also show the total effect of other variables on colorectal surgery complications.

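### Closeout nutrition status reflects supplementation given by indication, and the plan does not guarantee adjustment for baseline malnutrition, so the secondary nutrition-complication and mediation estimates may be confounded

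*Protocol article*

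**What the plan says.** The section Preoperative Nutritional Supplementation separates this care from the trial: "Nutritional supplementation will be carried out based on the risk of malnutrition and independently of the study protocol". The trigger is the PG-SGA: "In case of moderate or severe malnutrition, we will refer patients to nutrition consultation". The visit description under Study Period places the referral at visit 1 (baseline): "If malnutrition is detected, we will refer the patient to nutrition consultation". Referred patients stay on the study product for the same 4-6 weeks.

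Nutrition is assessed at visit 1 and again at closeout (Table 1). Under Nutritional Evaluation, "Nutritional status assessment will be based on the PG-SGA survey and albumin, prealbumin, total lymphocytes, and hemoglobin levels", with anthropometry in addition.

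The fourth secondary objective in the Introduction is the effect of the microbiome, inflammatory pattern and nutrition status on complications. Inferential Statistics plans a univariate screen, then a multivariable regression on the variables found significant, then a causal mediation analysis: "We will include as mediators the variables related to complications after surgery".

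On other data, the weekly call is described thus: "We will use this weekly phone call to collect data about adverse effects and treatment compliance". For discharge: "Data collection will include information about antibiotic prophylaxis used, length of stay, vital status, surgery performed, and final staging of the CRC". Receipt of nutritional supplementation is not among the items named.

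**The concern.** Supplementation goes to the patients who start worst nourished, and it acts before the second nutrition measurement. Their closeout values may rise while the surgical risk that goes with their baseline condition remains. Closeout status, or change in status, is then partly a marker of who was treated.

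Randomisation does not help here. The relation of nutrition to complications, and the mediator-outcome part of the mediation model, are observational even inside a randomised trial. They need the common cause, baseline malnutrition, in the model. The stated rules leave that to chance: a covariate enters if it passes a significance screen, and a mediator enters if it is associated with the outcome. At stake is the reading of one secondary objective and of any indirect effect through nutrition.

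**Working it through.** **No plan figure to reproduce.** The article gives no malnutrition prevalence, no uptake of supplementation and no expected nutritional gain. What follows is an illustration on assumed values.

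**Inputs**
- From Sample Size: 64 per arm before the dropout allowance, so n = 2 × 64 = 128.
- Assumed: 20% or 30% malnourished at baseline; complication odds ratio 2.5 for malnourished against well nourished; malnourished patients 1.2 SD lower at baseline; baseline-closeout correlation 0.8 within class; 27% complication risk in the well nourished; a supplementation gain g of 0, 0.5, 1.0 or 1.5 SD in the malnourished.
- By construction, risk depends on baseline class only. Closeout status has no effect of its own, so its true conditional odds ratio is 1.0.

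**Plausibility of the risk level.** Odds in the well nourished are 0.27/0.73 = 0.370; times 2.5 gives 0.925, a risk of 0.925/1.925 = 0.48. Overall risk is 0.27 + 0.2 × 0.21 = 0.31 or 0.27 + 0.3 × 0.21 = 0.33. The plan's 40% and 20% average 30%, so this is close.

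**Mechanism.** The class gap in closeout status is 1.2 − g: 1.2, 0.7, 0.2 and −0.3 SD for the four gains. It shrinks, nearly closes at 1.0 SD and changes sign at 1.5 SD. For change in status, the class gap is simply g.

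**Simulation** (logistic regression; ranges are over the two prevalences)

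| Gain in malnourished | OR per SD of closeout status, unadjusted | Same, with baseline class in the model |
|---|---|---|
| 0 | 0.81-0.84 | about 1.0 |
| 0.5 SD | 0.87-0.90 | about 1.0 |
| 1.0 SD | 0.96-0.97 | about 1.0 |
| 1.5 SD | 1.05-1.06 | about 1.0 |

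The unadjusted figure depends on the gain; the adjusted one does not. The unadjusted value is already off at zero gain, because baseline class alone links low closeout status to complications.

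**Would the significance screen bring baseline class in?** Chi-square approximation, two-sided 5%, z = difference / √[p̄(1 − p̄)(1/n₁ + 1/n₂)], with a risk difference of 0.48 − 0.27 = 0.21:
- 20% malnourished (25.6 against 102.4): √(0.31 × 0.69) × √(1/25.6 + 1/102.4) = 0.463 × 0.221 = 0.102; z = 2.06; power Φ(2.06 − 1.96) ≈ 0.54.
- 30% malnourished (38.4 against 89.6): 0.471 × 0.193 = 0.091; z = 2.31; power Φ(2.31 − 1.96) ≈ 0.64.

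So even with an odds ratio of 2.5, baseline class would fail the screen in roughly 36% to 46% of trials.

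**Against the noise.** The standard error of the unadjusted log odds ratio is about 0.19, a 95% interval factor of exp(1.96 × 0.19) ≈ 1.45 each way. A 0.5 SD gain shifts the log odds ratio by ln(0.90/0.84) ≈ 0.07, about a third of one standard error. The full range from 0.81 to 1.06 is ln(1.06/0.81) ≈ 0.27, about 1.4 standard errors.

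**The case against.** The best case against the point has four parts.

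*The article is condensed.* A form item for a concomitant treatment and the covariate list of an exploratory model are things an article may leave to fuller documents. The discharge list says what data collection will include, so it is not closed. Keeping routine care independent of the protocol does not say that receipt goes unrecorded. This stands: the absent supplementation item is not treated here as an error. What remains is the rule the article does state, adjustment by univariate significance only.

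*The confounder is measured.* A reader might infer that the trial has no variable with which to detect or correct the problem. The documents do not support that. Referral follows the PG-SGA, and the PG-SGA is collected at visit 1 and closeout. Only receipt, type and dates of supplementation are not listed.

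*The harm is easily overstated.* A reader might infer that supplementation would pull a real nutrition effect to nothing. The illustration does not show this. Closeout status has no effect of its own in it, so a drift from 0.81 towards 1.0 moves towards the truth, and reversal needs a gain above about 1 SD within 4-6 weeks. The shift at modest gains is also small beside sampling error; even with no gain, the unadjusted association reached P<.05 in only 14-19% of replicates.

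*The link is conditional.* Inferential Statistics does not say whether baseline, closeout or change in nutrition enters the regression, and it speaks of dietary patterns where the objective speaks of nutrition status. If only baseline status is used, later supplementation is a downstream co-treatment, not a confounder. Nutrition enters the mediation analysis only if found related to complications. This is why the point says that the estimate may be confounded.

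A reader might also extend the point to the primary endpoint. That does not follow: referral depends on a baseline score in a double-blind trial, so it should balance between arms apart from chance.

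**Conclusion.** The point holds as a limited one. Closeout and change in nutrition status reflect treatment given by baseline malnutrition, and neither the significance-only regression nor the association-based choice of mediators guarantees adjustment for that baseline state. The affected estimates are secondary and observational; the randomised comparison of complication rates stands.

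The size of any bias cannot be taken from the article. Under the assumed values it spans an odds ratio per SD of about 0.81 to 1.06 around a true value of 1.0, and including baseline class removes it at every gain tried. This rests on the assumed prevalence, odds ratio and gains, and on risk depending on baseline class alone. In that setting an indicator for supplementation adds nothing material beyond class. The point is minor in weight, but the correction uses data already planned.

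**What to change.** In Inferential Statistics, state that baseline PG-SGA class is a prespecified covariate, kept regardless of its univariate significance, in (a) the regression of complications on nutrition status wherever closeout or change values are used, and (b) the mediator-outcome model when a nutrition variable is a mediator. State as well which nutrition measurement (baseline, closeout or change) each model uses.

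Optionally, record at closeout whether nutrition consultation took place and whether supplementation was given, with type and dates, for description and a sensitivity analysis.

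The cost is one model term from data already collected at visit 1, a sentence or two of text and, if the option is taken, one form item. Clinical care is unchanged.

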### Sample Size

We designed the study on the basis that the complication rate in the nonintervention arm is 40% and that a 50% reduction would be clinically relevant. Assuming a β error of .80 and an 𝛼 error of .05, 64 patients should be included in each arm. Accounting for a dropout rate of 10%, it would be necessary to include a total of 144 patients (72 patients in each group). The sample size calculation was performed with the Ene 3.0 (GlaxoSmithKline SA) statistical software. A medical doctor will explain the benefits of participating in the study to the patients at the digestive oncology consultation to reach the target sample size.

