## Introduction

Colorectal cancer (CRC) is one of the most common malignancies in western countries. In 2018, about half a million cases were diagnosed in Europe, and 250,000 of those affected died due to this disease [1]. Most of the CRCs diagnosed are candidates for surgical resection with curative intent. Cure rates after surgery vary from 92% to 67% depending on the tumor stage [2]. However, colorectal surgery is associated with some life-threatening complications. There are several risk factors associated with these postoperative complications: age, sex, comorbidities, surgery urgency, tumor location, type of surgical approach, and surgical and hospital volume. Postoperative complications are detected during admission in 30% to 40% of patients who have had colorectal surgery [3-6]. Further, one study reported a lower percentage in the month after discharge (15%) and in the first year after surgery (25%) than at other times [3]. The most common complications are anastomotic failure, intra-abdominal infection, prolonged ileus, surgical site infection, deep vein thrombosis, pulmonary complications, and cardiac complications [6]. To assess the severity of surgical complications, different scales are available but the Clavien-Dindo classification is the most used in all parts of the world [7].

Some interventions have been proposed to reduce complications associated with colorectal surgery. Preoperative intravenous antibiotic prophylaxis is commonly used for the prevention of infectious postoperative complications [8]. The most appropriate regimen for antimicrobial prophylaxis for colorectal procedures and the optimal choice of antimicrobial agent have not been fully resolved. However, the last consensus international guidelines on antimicrobial prophylaxis recommend agents with activity against the anaerobic and aerobic floras of the bowel administered within 60 minutes before surgical incision [9]. Studies have shown that oral antibiotic administration can also reduce the risk of infections associated with surgery [10,11]. Other studies, however, have shown that this type of intervention does not modify the mortality and severity of other complications detected [12,13].

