#### Inferential Statistics

We will apply inferential statistics to identify differences between the control and experimental groups. In general, dichotomous variables will be compared with chi-square tests, whereas qualitative variables with more than 2 categories will be compared with analysis of variance tests. Continuous variables will be compared with *t* tests for independent samples or Mann-Whitney *U* tests if they do not meet normality. *P*<.05 will be considered statistically significant. More specifically, to analyze the outcomes of the study the following statistical methodology will be performed:

We will analyze the complication rate after surgery in the 2 intervention groups. We will base this analysis on severity and type of complication. After stratification by tumor location, we will use chi-square tests to identify significant differences between the 2 groups. Risk ratio and 95% confidence interval will be used to describe the differences found.We will describe adverse events reported in each group. To find significant differences between the 2 groups, chi-square tests will be used after stratification by tumor location. Risk ratio and 95% confidence interval will be used to describe the differences found.Diversity and composition of the gut microbiota will be analyzed in the 2 groups using McNemar tests and *t* tests to identify significant differences between the groups.Inflammatory differences between the 2 intervention groups will be analyzed with *t* tests if variables meet normality or Wilcoxon tests if variables do not meet normality. We will also analyze the dynamic changes of the neutrophil-lymphocyte ratio in the 2 intervention groups.Differences in dietary pattern and quality of life will be analyzed with McNemar tests for qualitative variables and *t* tests for quantitative data.We will perform a univariate analysis to identify any associations between impact of the microbiome, inflammatory and dietary patterns, and surgery complications. We will perform a multivariate regression with the significant variables found. In addition, the model fit will be assessed using a likelihood-ratio test, area under the receiver operating characteristic curve, Akaike information criterion, and Bayesian information criterion, and we will then validate the model designed using the bootstrap method.

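### The 64 per arm matches a one-sided calculation; the planned chi-square test has about 70% power for 40% versus 20%, not 80%

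*Protocol article*

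**What the plan says.** The Sample Size section of the protocol article rests the trial on two assumptions: that "the complication rate in the nonintervention arm is 40"%, and that "a 50% reduction would be clinically relevant". The comparison is therefore 40% versus 20%. The error rates are introduced with "Assuming a β error of .80" and an alpha of .05, and the result is that "64 patients should be included in each arm". An allowance of 10% for dropout raises this to 72 per arm, 144 in total. The section does not say whether the test is one-sided or two-sided.

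The Inferential Statistics section compares complication rates between the groups with chi-square tests after stratification by tumor location. The threshold is P"<.05 will be considered statistically significant". For the estimate, "Risk ratio and 95% confidence interval will be used to describe the differences found". The article mentions no one-sided test or one-sided significance level.

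On the control rate, the Introduction states: "Postoperative complications are detected during admission in 30% to 40% of patients who have had colorectal surgery".

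**The concern.** A two-sided comparison of 40% with 20% at the usual 5% level and 80% power needs roughly 80 patients per arm, so 64 looks too small. If 64 comes from a one-sided calculation while the analysis uses a test that rejects in either direction, the trial has been sized for a different test from the one it will run.

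This calculation is the only justification given for 144 patients, and it concerns the primary endpoint. If the real power is well below 80%, a non-significant result is weaker evidence against the supplement than readers would take it to be.

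**Working it through.** **Inputs.** From Sample Size: p1 = 0.40, p2 = 0.20, alpha = .05, power = 0.80 (the only reading of the .80 that fits 64), dropout 10%. From Randomization: 1:1 allocation. From Inferential Statistics: chi-square test at P<.05.

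**Formula.** With p̄ = (p1 + p2)/2 = 0.30, the number per arm for comparing two proportions (pooled variance under the null) is

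n = [z_α √(2p̄(1−p̄)) + z_β √(p1(1−p1) + p2(1−p2))]² / (p1−p2)²

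Here √(2 × 0.30 × 0.70) = √0.42 = 0.6481, √(0.24 + 0.16) = √0.40 = 0.6325, z_β = 0.8416 and (p1−p2)² = 0.04.

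**Step 1: reproduce the plan's figure.** One-sided, z_α = 1.6449:

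n = (1.6449 × 0.6481 + 0.8416 × 0.6325)² / 0.04 = (1.0660 + 0.5323)² / 0.04 = 63.9, so 64 per arm.

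Dropout: 64/0.9 = 71.1, so 72 per arm and 144 in total. Both figures match the article, so the dropout step is correct and the problem lies wholly in the 64.

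**Step 2: the same inputs, two-sided.** z_α = 1.9600:

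n = (1.2702 + 0.5323)² / 0.04 = 81.2, so 82 per arm. Dropout: 82/0.9 = 91.1, so 92 per arm and 184 in total.

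**Step 3: could another formula give 64?**

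| Variant | One-sided | Two-sided |
|---|---|---|
| Pooled variance under the null | 64 | 82 |
| Unpooled variance | 62 | 79 |
| Pooled variance under both hypotheses | 65 | 83 |
| Arcsine | 64 | 81 |
| Pooled with continuity correction | 74 | 91 |

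Every two-sided variant gives 79 or more, so neither rounding nor choice of formula explains 64.

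**Step 4: power of the two-sided test.** Power = Φ{[|p1−p2|√n − 1.96√(2p̄(1−p̄))] / √(p1(1−p1) + p2(1−p2))}. At n = 64 this is Φ[(0.20 × 8 − 1.2702)/0.6325] = Φ(0.521) = 69.9%.

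| Evaluable per arm | Normal approximation | Exact enumeration, uncorrected chi-square | Exact enumeration, continuity-corrected |
|---|---|---|---|
| 64 | 69.9% | 70.7% | 63.0% |
| 72 (no dropout) | 75.0% | 75.7% | 69.6% |
| 82 | 80.4% | 80.7% | 75.9% |

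**Step 5: what 64 per arm can detect.** Solving the power formula for p2 with p1 = 0.40 and 80% power gives p2 = 0.178, a relative reduction of 1 − 0.178/0.40 = 56%.

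**Step 6: sensitivity to the control rate.** With 64 per arm and the rate still halved, power is 61.6% for 35% versus 17.5% and 52.9% for 30% versus 15%.

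**The case against.** The arithmetic is not in dispute. The strongest objections concern what is inferred around it.

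- **Sidedness is never stated.** The article prints neither one-sided nor two-sided, and the settings used in the sample-size software are not shown. That 64 came from a one-sided calculation is inferred from the exact match. The match is not unique: a two-sided t-test for a standardised difference of 0.5 also gives 64 per arm, although it would be the wrong method for a complication rate. This stands as a caution about the origin of the 64. It does not change the shortfall, which is the same however the number arose.
- **The hypothesis is directional, and a fuller document might declare a one-sided test.** The trial does expect fewer complications. But a chi-square test of differences at P<.05, reported with a 95% confidence interval, is non-directional by ordinary reading. If a one-sided test was meant, the analysis section describes a different test. Either way, the sample-size and analysis sections disagree.
- **The 40% control rate lies within the range the article gives.** This is fair. It is the top of 30% to 40%, and enrolment is limited to ASA class I or II, but the article gives no rate specific to such patients. The 35% and 30% scenarios are context, not an error in the plan.
- **The β label is a slip.** Agreed: 80% power is the only reading compatible with 64, so the label has no numerical consequence.
- **The 70% ignores stratification.** It refers to one overall table of 64 versus 64. Separate tests within tumor-location strata would have less power, so this does not favour the plan.

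**Conclusion.** The concern holds. For 40% versus 20%, 64 evaluable patients per arm give a two-sided 5% chi-square test about 70% power (69.9% by the normal approximation, 70.7% by exact enumeration), falling to 63% with a continuity correction. Full retention of 72 per arm raises the uncorrected figure only to about 75%. The false-negative risk for the stated effect is about 30%, half as large again as the 20% intended.

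This rests on three assumptions: the .80 means power, the primary comparison is the overall two-arm one, and the chi-square test at P<.05 is two-sided. The last is inferred from the test and the interval, since the article does not state it.

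**What to change.** Keep 144 patients and correct the Sample Size section, for example:

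> With 64 evaluable patients per arm, a two-sided chi-square test at alpha .05 has about 70% power (beta about .30) to detect 40% versus 20%, and 80% power to detect 40% versus about 18%.

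State the sidedness explicitly there and in Inferential Statistics, and replace the β error of .80 with the correct term. As useful context, add the power at control rates of 35% (about 62%) and 30% (about 53%), assuming the rate is halved.

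This costs only wording in the protocol and analysis plan and needs no extra patients; the price is a less favourable power statement. It discloses the shortfall but does not remove it. Restoring 80% power for 40% versus 20% with the uncorrected two-sided test would take 82 evaluable patients per arm, or 184 randomized after 10% dropout: 40 more than planned.
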